## Abstract

**Background:**

Patients with stable chest pain suspected of coronary artery disease (CAD) usually undergo multiple diagnostic tests to confirm or rule out obstructive CAD. Some tests may not effectively assess the presence of CAD, precluding optimal treatment. A diagnostic strategy of upfront computed tomography coronary angiography (CTCA) combined with optimal medical therapy (OMT) tailored to the extent of CAD may be superior to standard care in preventing major adverse cardiac events.

**Study design:**

The CLEAR-CAD trial is a prospective, open-label, multicentre, randomised, superiority trial of an upfront CTCA-guided strategy in 6444 patients presenting in an outpatient setting with suspected CAD compared with standard care, in approximately 30 participating centres in the Netherlands. The upfront CTCA-guided strategy consists of an initial CTCA which is assessed using the Coronary Artery Disease-Reporting and Data System (CAD-RADS 2.0). In patients without CAD (CAD-RADS 0) no specific cardiac medication is mandated. Patients with non-obstructive CAD (CAD-RADS 1–2) are treated with preventive OMT. Patients with obstructive CAD (CAD-RADS ≥ 3) are treated with preventive and anti-anginal OMT; in the presence of pharmacologically refractory symptoms patients undergo selective revascularisation after non-invasive functional imaging for myocardial ischaemia (≥ 10%). Patients with significant left main or proximal left anterior descending coronary artery stenosis on CTCA undergo direct invasive coronary angiography and subsequent revascularisation. The primary endpoint is the composite of all-cause death and myocardial infarction.

**Conclusion:**

The CLEAR-CAD trial is the first randomised study to investigate the efficacy of a combined upfront CTCA-guided medical and selective revascularisation strategy in an outpatient setting with suspected CAD compared with standard care.

**Supplementary Information:**

The online version of this article (10.1007/s12471-024-01906-3) contains supplementary material, which is available to authorized users.

## Introduction and rationale

In clinical practice, patients with stable chest pain suspected of coronary artery disease (CAD) still undergo a variety of diagnostic tests [1, 2]. These may include exercise electrocardiogram (X-ECG), (stress) echocardiography, computed tomography coronary-artery calcium score (CAC), computed tomography coronary angiography (CTCA), nuclear imaging, cardiac magnetic resonance (stress perfusion) imaging (CMR) and invasive coronary angiogram (ICA) with invasive coronary physiology or imaging. All these tests have inherent limitations, leading to potential false-positive and/or false-negative results with additional visits for downstream tests [3]. In addition, most tests do not detect non-obstructive CAD, precluding many patients from optimal primary preventive therapy. Also, many patients with positive functional testing undergoing ICA do not have obstructive CAD [4].

In the SCOT-HEART trial, the routine use of CTCA on top of standard care in the assessment of stable chest pain increased the frequency and accuracy of CAD diagnosis. The improved detection of both obstructive and non-obstructive CAD allowed targeted preventive optimal medical therapy (OMT), which is assumed to have driven the significant reduction of death from coronary heart disease and nonfatal myocardial infarction (MI) at 5‑year follow-up [5]. Currently, the European Society of Cardiology (ESC) guidelines recommend non-invasive functional imaging or CTCA as the initial diagnostic test in most patients with stable symptoms suspected of CAD [6].

The SCOT-HEART trial did not explore a CTCA-first strategy, as CTCA was added to standard care [7]. CTCA on top of standard care resulted in an increased number of total diagnostic tests in the CTCA group, leading to higher direct healthcare costs within the first 6 months [8]. Besides, there was no reduction in the number of diagnostic ICAs observed [5]. Thus far, an upfront CTCA-guided strategy for the combined diagnosis and treatment of suspected CAD has not been studied in comparison with standard care. In the DISCHARGE trial, patients with stable chest pain referred for ICA were randomised to either CTCA or ICA and showed similar major adverse cardiovascular events (MACE) rates over 3.5 years follow-up [9].

Moving from diagnosis to treatment, the ISCHEMIA and REVIVED trial showed that OMT was non-inferior to an early invasive strategy plus OMT with regard to the primary clinical outcome in patients with obstructive CAD and proven ischaemia on non-invasive imaging or exercise test without imaging [10, 11]. Therefore, ICA and revascularisation can safely be withheld in most patients and only used in a small subset of patients with pharmacological refractory symptoms.

To combine the evidence and overcome limitations of previous trials, a new randomised trial testing an upfront CTCA-guided strategy for the combined diagnosis and treatment of suspected CAD was warranted [5, 9–11]. These observations led to the design of the ‘Clinical Outcomes and Cost-effectiveness of a Diagnostic and Treatment Strategy of Upfront CTCA plus Selective Non-Invasive Functional Imaging Compared with Standard Care in Patients with Chest Pain and Suspected Coronary Artery Disease’ (CLEAR-CAD) trial. The study hypothesis is that an upfront CTCA-guided strategy combined with OMT and highly selective revascularisation, after non-invasive functional imaging for detection of myocardial ischaemia (≥ 10%) in patients with obstructive CAD and pharmacological refractory symptoms, reduces MACE.

## Methods

### Study design and population

The CLEAR-CAD trial is a prospective, open-label, multicentre, randomised clinical trial enrolling 6444 patients referred to a cardiology outpatient clinic with stable chest pain suspected of CAD. The study specifically excludes patients with a history of CAD on cardiac imaging or those suspected of having acute coronary syndrome. The inclusion and exclusion criteria are presented in Table 1. Patients are selected for inclusion in the study at the end of the first visit to the outpatient clinic, and consenting patients are randomised in a 1:1 ratio to either the upfront CTCA-guided strategy or standard care (Fig. 1).

**Table 1 Tab1:** Inclusion and exclusion criteria

Inclusion criteria	Exclusion criteria
- Outpatient presentation to the cardiologist with stable chest pain suspected for CAD and ≥ 18 years	- Presentation with or history of acute coronary syndrome (STEMI/NSTEMI/unstable angina) - History of CAD on cardiac imaging^a^ - History of PCI and/or CABG - Permanent atrial fibrillation - Severe renal failure (eGFR < 30 ml/min) - Severe allergy to iodinated contrast medium - Known pregnancy - Patients with an estimated life expectancy of less than 1 year

*CABG* coronary artery bypass grafting, *CAD* coronary artery disease, *CTCA* computed tomography coronary angiography, *eGRF* estimated glomerular filtration rate, *ICA* invasive coronary angiogram, *NSTEMI* non-ST-segment elevation myocardial infarction, *PCI* percutaneous coronary intervention and STEMI ST-segment elevation myocardial infarction

^a^History of CAD on cardiac imaging is defined as the presence of coronary calcifications on a coronary-artery calcium score, or as either non-obstructive or obstructive CAD detected by CTCA or ICA, or a positive functional test detected with dobutamine stress echocardiography, stress cardiac magnetic resonance imaging, single-photon emission computed tomography, or positron emission tomography

**Fig. 1 Fig1:**
[figure not shown]
Study design (*CAC* coronary-artery calcium score, *CAD* coronary artery disease, *CTCA* computed tomography coronary angiography, *OMT* optimal medical therapy)

### Study procedures

#### Upfront CTCA-guided strategy

Patients randomised to the upfront CTCA-guided strategy (intervention) undergo CTCA (+CAC) within 6 weeks after randomisation (Fig. 2). The CTCA is assessed using the standardised Coronary Artery Disease-Reporting and Data System (CAD-RADS 2.0) method [12]. The subsequent diagnostic and treatment strategies are based on the CAD-RADS score:In patients with CAD-RADS 0, CAD is excluded as the cause of anginal chest pain. In these patients no specific cardiac medication is mandated.In patients with CAD-RADS 1–2, CTCA indicates non-obstructive CAD, excluding obstructive CAD as the cause of anginal chest pain. In these patients, preventive OMT is started, consisting of a lipid-lowering drug. Initiation of platelet aggregation inhibition is at the discretion of the treating cardiologist.In patients with CAD-RADS ≥ 3, CTCA indicates obstructive CAD. In these patients, the treating cardiologist starts preventive OMT consisting of both a lipid-lowering drug and a platelet aggregation inhibitor and additional anti-anginal medication (OMT+) consisting of a minimum of one of the following: beta-blocker, long-acting nitrate or calcium channel blocker. After 4–6 weeks, anginal symptoms will be evaluated by the cardiologist. In the event of persistent symptoms, additional non-invasive functional imaging will be performed within 3 months. Patients qualify for ICA in the presence of either myocardial ischaemia in at least 10% of the myocardium on nuclear perfusion via SPECT/PET or CMR stress perfusion imaging or at least 2 of 16 segments with severe hypokinesis or akinesis on stress echocardiography. In the absence of ischaemia as defined above and persisting symptoms under optimised medical therapy, ICA may be considered.In CAD-RADS ≥ 3 patients, a high-risk anatomy is defined as having left main (LM) diameter stenosis of at least 50% and/or a proximal left anterior descending (LAD) diameter stenosis of at least 70%. These patients do not require non-invasive ischaemia detection but are sent for direct ICA and subsequent revascularisation.In patients with CAD-RADS *N*, CTCA indicates a (partial) non-diagnostic examination. Management of these patients is described in Appendix C of the Electronic Supplementary Material.

**Fig. 2 Fig2:**
[figure not shown]
The intervention group (CTCA-guided) (*CAD-RADS* Coronary Artery Disease-Reporting and Data System, *CT* computed tomography, *ICA* invasive coronary angiography, *LAD* left anterior descending artery, *OMT* optimal medical treatment)

Initiation of medical treatment is allowed before CTCA.

#### Standard care strategy

Patients randomised to the standard care strategy (control) are diagnosed and treated according to the current standard care as outlined in the ESC guidelines for suspected CAD [6]. In current practice, X‑ECG, CAC, CTCA, non-invasive functional imaging tests and ICA are used interchangeably [1, 2]. A slow uptake of CTCA scans in the control group is anticipated during the study [13]. The assessment of CTCA is similar in both groups. Initiation of medical treatment is allowed at any time.

### Data collection and follow-up

All data, including the initial diagnostic trajectory and treatment, are documented in the case report forms (CRF) of the web-based electronic data capture system Castor. Follow-up is performed by telephone at 1, 3, 6 and 12 month(s) and every other year until follow-up at 5 years has been completed in all patients. In the event of the suspected occurrence of clinical endpoints, full source clinical data are collected from the hospital and general practitioners.

Assessment of symptoms of angina, dyspnoea and quality of life are assessed by the Seattle Angina Questionnaire (SAQ), the Rose Dyspnea Scale, and the EuroQol-5D (EQ-5D-5L) at the corresponding follow-up time points. Patients are also asked to complete the Institute for Medical Technology Assessment (iMTA), Medical Consumption Questionnaire (iMCQ) and the Productivity Cost Questionnaire (iPCQ) at 3, 6 and 12 months and every other year until follow-up at 5 years has been completed in all patients. All questionnaires are sent by email or post.

### Study endpoints and statistical analysis

#### Primary endpoint

The primary endpoint is the composite of all-cause death and MI according to the fourth Universal definition [14]. The main analyses of the primary endpoint are based on the time from randomisation to the first occurrence of any component of the primary endpoint. These analyses are performed in the full analysis population of all randomised patients under application of the intention-to-treat principle, which means events are counted irrespective of their occurrence relative to implementation of the randomised strategy (upfront CTCA or control). Kaplan-Meier estimates of cumulative risk and cumulative hazard functions are provided to evaluate the timing of event occurrence in the different treatment groups and the consistency of the respective treatment effects for all time points. The hazard ratio (HR), of upfront CTCA versus standard care, and corresponding two-sided 95% confidence intervals (CIs) are estimated based on Cox proportional hazards models.

The study was designed to test the following hypotheses in this hierarchical order to preserve type 1 error rate; (i) the upfront CTCA-guided strategy is non-inferior to standard care in terms of the primary endpoint, (ii) the upfront CTCA-guided strategy is superior to standard care in terms of the primary endpoint.

Non-inferiority of the upfront CTCA regimen (vis-à-vis standard care) in terms of the primary endpoint is declared if the 95% CI of the HR excludes 1.62. Superiority of the upfront CTCA regimen (vis-à-vis standard care) in terms of the primary endpoint is declared if the 95% CI of the HR excludes 1, which is equivalent to *p* < 0.05 for the log-rank test. Use of 95% CI is equivalent to non-inferiority testing with a one-sided type I error (*α*) of 0.025 and to superiority testing with a two-sided type I error rate of 0.05.

Based on the literature, the cumulative incidences at 3 years were estimated at 3.0% (control) and at 1.75% (intervention) respectively [5]. Because of an anticipated greater use of CTCA up to 30% in the control group, we estimated that a 3-year event rate in the control group would be equal to 2.82%. Assuming an exponential distribution, a target relative risk at 3 years of 0.6206 (a reduction of the 3‑year cumulative incidence from 2.82 to 1.75%) corresponds to a HR of 0.617. With 5900 fully evaluable patients and a median duration of follow-up of 3 years, the study is designed with 80% power to demonstrate the superiority of the upfront CTCA-guided strategy over standard care. The study is event-driven and the primary analysis will be performed when the number of 135 events has been reached. Follow-up is censored at the last date of known outcome status for the occurrence of death or myocardial infarction or at the global end-of-study date, which is defined as the day of occurrence of the 135 events. To account for an expected rate of lost to follow-up of 5–7%, this study will enrol 6444 patients. With a total of 135 primary endpoints, the study has a 80% power to show non-inferiority of the upfront CTCA-guided strategy to standard care, using a non-inferiority margin of 1.62 for the HR. The non-inferiority margin of 1.62 is approximately equal to the inverse of the expected therapeutic benefit (1.0/0.617).

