## Discussion

The multicentre, randomised, clinical CLEAR-CAD trial aims to evaluate an upfront CTCA-guided strategy in 6444 patients presenting with stable chest pain suspected of CAD. The upfront CTCA-guided strategy is combined with optimal medical therapy and highly selective revascularisation after non-invasive functional imaging for detection of myocardial ischaemia in patients with obstructive CAD and pharmacological refractory symptoms. This study aims to demonstrate superiority of the upfront CTCA-guided strategy on the composite primary endpoint of all-cause death and MI compared with standard care.

It is common knowledge that CTCA is able to accurately rule out CAD with an overall sensitivity of 95%, rendering it an excellent first-line test for patients with stable chest pain suspected of CAD [20]. Landmark CTCA trials have demonstrated that the use of CTCA in these patients resulted in higher diagnostic yield for detecting CAD [7, 9, 21]. The early diagnosis of both obstructive and non-obstructive CAD allows to guide and intensify preventive medical therapy, thereby potentially reducing future cardiovascular events [5].

CLEAR-CAD is unique as none of the previous CTCA trials investigated a combined upfront CTCA-guided medical and selective revascularisation strategy compared with standard care (Table 3 for the landmark CTCA trials [5, 7, 9, 21] and Table S1 of the Electronic Supplementary Material for all the randomised CTCA trials [5, 7, 9, 21–32]).

**Table 3 Tab3:** Landmark randomised CTCA trials in patients with stable chest pain suspected of CAD

Study, (year)	*N*	Design		Known CAD excluded	Patients (PTP)	Standardised CTCA reporting	Prespecified medical strategy in CTCA group	Prespecified invasive strategy in CTCA group	Primary endpoint	Results
		Intervention	Control							
PROMISE, (2015)	10003	CTCA	Functional imaging	No^a^	Low to intermediate, 53.4 ± 21.4 vs 53.2 ± 21.4^b^	No	No	No	All-cause death, MI, hospitalisation for unstable angina, or complications (FUP median 25 months)	3.3% vs 3.0% *p* = 0.75
SCOT-HEART, (2015)	4146	Standard care +CTCA (+CAC)	Standard care	No^c^	Low to intermediate, 18 ± 11 vs 17 ± 12^d^	No	No	No	Certainty of angina diagnosis caused by CAD at 6 weeks	HR 1.79 (1.62–1.96); *p* < 0.0001
SCOT-HEART, (2018)^e^									Death from CAD or MI (FUP 5 years)	2.3% vs 3.9% *p* = 0.004

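### The planning HR of 0.617 appears to be an undiluted effect on coronary death or MI, so the 80% superiority power is not supported for all-cause death or MI

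*Protocol article*

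**What the plan says.** All of this is in the protocol article.

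- **Endpoint of this trial** (Primary endpoint): "The primary endpoint is the composite of all-cause death and MI according to the fourth Universal definition". Table 2 repeats it and ranks cardiovascular death or MI as a separate secondary endpoint.
- **Source of the planning rates** (Primary endpoint, sample-size paragraph): "Based on the literature, the cumulative incidences at 3 years were estimated at 3.0% (control) and at 1.75% (intervention) respectively [5".
- **Endpoint of that source.** The Introduction credits it with a "significant reduction of death from coronary heart disease and nonfatal myocardial infarction (MI" reduction at 5 years. Table 3 in the Discussion lists "Death from CAD or MI (FUP 5 years", with 2.3% against 3.9%. The article gives no other clinical endpoint for reference [5].
- **Adjustment.** Anticipating up to 30% CTCA use in controls, the sponsor lowers the control rate: "we estimated that a 3-year event rate in the control group would be equal to 2.82" per cent. No other allowance is described.
- **Result.** The reduction from 2.82% to 1.75% "corresponds to a HR of 0.617", and "the study is designed with 80% power to demonstrate the superiority of the upfront CTCA-guided strategy over standard care". The primary analysis is triggered by 135 events.

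**The concern.** A strategy that works through coronary diagnosis and preventive treatment is expected to act on coronary death and MI. A composite that counts all deaths also contains events, such as cancer deaths, on which little or no effect is expected. Eligibility runs from 18 years with no upper age limit, and the only exclusion tied to survival is a life expectancy under 1 year, so such deaths will occur. Each one counts towards the 135 and pulls the overall HR towards 1. If the planning HR belongs to the coronary endpoint, the trial has less superiority power than stated.

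More than the primary test is at stake. The ranked secondary endpoints are tested only if superiority on the primary endpoint is shown. A diluted primary result would therefore also block the formal test of cardiovascular death or MI, which is closer to the effect seen in the source. A neutral primary result could be read as no benefit when the trial had too little power to show a coronary benefit of the planned size.

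**Working it through.** **1. Reproduce the plan.** Inputs from the sample-size paragraph: 2.82% and 1.75% at 3 years, exponential times, 1:1 allocation, two-sided α 0.05, 135 events.

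- HR = ln(1 − 0.0175) / ln(1 − 0.0282) = 0.617.
- Events for 80% power (Schoenfeld) = 4(1.96 + 0.8416)² / (ln 0.617)² = 134.6, so 135.
- Power at 135 events = Φ(½√135 × |ln 0.617| − 1.96) = Φ(5.81 × 0.4829 − 1.96) = 80.1%.
- Expected events in 5900 patients at 3 years = 2950 × (0.0282 + 0.0175) = 134.8.
- Non-inferiority at true HR 1, margin 1.62: Φ(5.81 × ln 1.62 − 1.96) = 80.0%.

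Every stated figure is confirmed.

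**2. Compare the planning effect with the source.**

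- Planning rates before the CTCA adjustment: ln(1 − 0.0175) / ln(1 − 0.030) = 0.580.
- Table 3, coronary death or MI at 5 years: ln(1 − 0.023) / ln(1 − 0.039) = 0.585.

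The relative effects almost coincide. The absolute rates do not: constant-hazard scaling of Table 3 to 3 years gives 1 − 0.961^0.6 = 2.36% and 1 − 0.977^0.6 = 1.39%, below 3.0% and 1.75%.

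**3. Dilute the effect.** Let s be the share of control-arm primary events that are non-coronary deaths. Assume no effect on these and HR 0.617 on the rest. Then HR = (1 − s) × 0.617 + s. The documents do not give s, so a range is shown. Events available are those from 5900 patients each followed for 5 years, with the control rate held at 2.82% at 3 years.

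| s (assumed) | HR | Superiority power at 135 events | Events needed for 80% | Events available by 5 years |
|---|---|---|---|---|
| 0% | 0.617 | 80% | 135 | 223 |
| 5% | 0.636 | 75% | 154 | 226 |
| 10% | 0.655 | 69% | 176 | 228 |
| 20% | 0.694 | 57% | 235 | 233 |
| 30% | 0.732 | 44% | 323 | 239 |

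**4. Alternative model.** If 2.82% and 1.75% contain no non-coronary deaths, add the same 3-year non-coronary mortality q to both arms (again assumed): HR = [−ln(1 − 0.0175) − ln(1 − q)] / [−ln(1 − 0.0282) − ln(1 − q)].

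| q (assumed) | HR | Power at 135 events | Events needed | Events available by 5 years |
|---|---|---|---|---|
| 0.5% | 0.674 | 63% | 203 | 270 |
| 1.0% | 0.717 | 49% | 284 | 317 |
| 1.5% | 0.750 | 39% | 378 | 364 |

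**The case against.** **The calculation is not wrong.** The article declares a target effect and powers for it, and at that effect 135 events give 80.1%. This stands. A reader might infer that 135 events fail to deliver the stated power; the documents do not support that. What is open to question is whether 0.617 is a reasonable target for this endpoint.

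**The link to the coronary endpoint is partly inference.** The sample-size paragraph does not name the endpoint behind 3.0% and 1.75%, and the scaled Table 3 rates are lower. The planning rates may have been read from a curve, raised, or taken from another outcome. This stands as a limit on certainty, but it does not rescue the HR. If the rates were raised to include other deaths, the additions are 3.0 − 2.36 = 0.64 points in control and 1.75 − 1.39 = 0.36 in intervention. Their ratio is 0.56, so the added deaths were also assumed to fall by more than 40%.

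**The coronary effect may be larger here.** Table 3 shows no prespecified medical or invasive strategy in the source trial and both in this one. An overall HR of 0.617 would survive a coronary HR of (0.617 − 0.10) / 0.90 = 0.574 at a 10% share, or (0.617 − 0.20) / 0.80 = 0.521 at 20%. It is therefore not true that the power holds only if non-coronary deaths fall by 38%. The sample-size paragraph does not make this argument, though it could. A nil effect on every non-coronary death is also an assumption, since the group includes other cardiovascular deaths and the strategy includes lipid lowering.

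**Non-inferiority is tested first and its stated power is untouched.** This stands in full.

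**Follow-up need not shorten much.** A reader might infer that extra deaths bring the analysis forward substantially. That follows only in the additive model. With uniform accrual from September 2022 to the end of 2025 and 5900 patients, median follow-up at the 135th event falls from 3.0 to about 2.5, 2.1 and 1.8 years at q = 0.5, 1.0 and 1.5%. In the share model it is still about 2.9, 2.9 and 2.8 years at 10, 20 and 30%.

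**Conclusion.** The concern holds as a gap in justification. The planning HR appears to carry an effect on coronary death or MI over to all-cause death or MI without dilution, and control-arm CTCA use is the only thing allowed for. The 80% superiority power is therefore not supported for the chosen endpoint unless non-coronary deaths fall similarly or the coronary effect exceeds that of the source.

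The size is conditional. It rests on an assumed share of non-coronary deaths, no effect on them, HR 0.617 on the remainder, and proportional hazards. Under these assumptions, shares of 5 to 30% give power of about 75% down to 44% at 135 events, and even a 2% share gives 78%. The documents do not show which share applies, so no single figure can be called the true power.

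**What to change.** In the sample-size paragraph, do one of two things:

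- restate the superiority power for all-cause death or MI, applying 0.617 to the coronary part only, stating the assumed share of non-coronary deaths, and giving the resulting HR and power at 135 events; or
- justify 0.617 for this endpoint, for example by arguing that the prespecified treatment strategy gives a larger coronary effect than in the source.

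In either case, name the endpoint to which 3.0% and 1.75% refer. The assumed share can be checked without unblinding, because a blinded committee adjudicates all primary and secondary endpoints, including cardiovascular death; pooled adjudicated deaths are enough. The cost is one paragraph and a less favourable stated power.

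Optionally, raise the event trigger on blinded pooled data within the 5-year follow-up already planned. This needs no new patients, but it is not a sure remedy. At a share of about 20% or more, or added 3-year non-coronary mortality of about 1.5%, 5-year follow-up would not restore 80% power (235 events needed against about 233 available, and 378 against 364). Where it would work, the primary analysis may fall after the end of 2027, when results are now expected: with uniform accrual as above, a 10% share needs 176 events, reached in about early 2028.
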